## Introduction

The growing epidemic of cerebrovascular disease (CBD; eg, stroke) and cardiovascular disease (CVD; eg, myocardial infarction (MI)) now intersects with the HIV epidemic.^1^ Countries such as Malawi have an adult HIV prevalence of approximately 10%.^2^ There is an increased life expectancy among people living with HIV, largely because of the successful scale-up of antiretroviral therapy (ART).^3^ In Europe and the USA, HIV is associated with a 50% increased risk of CVD compared with HIV-uninfected populations,^4^ attributable to long-term ART use and HIV per se.^4 5^ HIV infection is also associated with a 1.8-fold increased risk of all-cause heart failure in US veterans.^6^ Our recent case–control study of stroke in Malawian adults is one of several examples that demonstrate a high risk of HIV infection associated with stroke and heart disease, pointing to a considerable and unappreciated CBD/CVD risk among patients with HIV in this setting.^7–10^

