## Methods and analysis

### Study design

To address objective 1, we will conduct a single-centre, 36-month, prospective cohort study in 800 HIV-infected patients initiating ART and 190 HIV-uninfected adults aged ≥35 years. HIV-infected and HIV-uninfected participants will be frequency-matched by 5-year age band and sex. On a 6-monthly basis, we will measure markers of viral infection, inflammation and endothelial function along with surrogate markers for CBD/CVD (table 1).

**Table 1 T1:** Laboratory tests and clinical procedures in ART patients and HIV-uninfected adults

	Study time points						
	Baseline	6 months	12 months	18 months	24 months	30 months	36 months
Clinical procedures							
PWV	X	X	X	X	X	X	X
CIMT	X				X		
ABPI	X	X	X	X	X	X	X
Cardiac echo (participant subset)	X				X		
ECG (participant subset)	X				X		
Cardiometabolic markers							
Creatinine Full blood count	X X	X			X		
Cholesterol (LDL, HDL, triglycerides)	X				X		
Serum glucose/haemoglobin A1c	X				X		
HIV infection and progression							
HIV viral load (patients with HIV)	X	X	X				
CD4 count (patients with HIV)	X	X	X				
HIV rapid test (controls)	X		X		X		X
Immune dysregulation							
Soluble markers of systemic inflammation	X	X	X				
Soluble markers of endothelial activation	X	X	X				
CD8 and CD4 T cell activation and senescence (participant subset)	X	X	X		X		X
Monocyte/Macrophage activation and senescence (participant subset)	X	X	X		X		X
Herpesviruses infection							
CMV IgG	X	X					
VZV IgG	X	X					

ABPI, Ankle Brachial Pressure Index; ART, antiretroviral therapy; CIMT, carotid intima-media thickness; CMV, cytomegalovirus; HDL, high-density lipoprotein; LDL, low-density lipoprotein; PWV, pulse wave velocity; VZV, varicella zoster virus.

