### Sample size and statistical analysis

The required sample size for the study’s primary objectives is 800 HIV-infected patients and 190 HIV-uninfected adults using standard, normal distribution approximation sample size formulas for comparing proportions in two groups of unequal size and based on the following assumptions: (1) of HIV-infected study participants, 18.4% have abnormal PWV at baseline. We will exclude these participants from analysis. The 18.4% figure is informed by our ongoing studies of vasculopathy in HIV-infected patients, where this is the percentage of participants aged ≥35 years who have a PWV (>12 m/s). (2) Of both HIV-infected patients and HIV-uninfected adults, 20% will be lost to follow-up, including by death and HIV seroconversion.^40 41^ (3) The minimum relative risk (RR) of interest is 2 for objective 1 and 1.8 for objective 2. (4) The 24-month cumulative risk of clinically significant vasculopathy over study follow-up is 18.4% in the HIV-positive group. This is based on the same study data cited in (1). (5) For objectives 2a–2c, the exposure prevalence for each risk factor is 20%. (6) Statistical tests will have 80% power based on a two-sided test with α=0.05. Testing of hypotheses for the secondary outcome will be exploratory. However, we estimate 26 strokes (4 mimics), an unknown number of MIs and 80 deaths occurring during the study.^7 42^ Taken together, assumptions (3), (4) and (5) mean that, for 80% power, we assume a 24-month cumulative vasculopathy risk of 9.2% in HIV-negative participants, 18.4% in all HIV-infected participants, 15.9% in HIV-infected participants not exposed to the risk factors from objectives 2a–2c and 28.6% in the HIV-infected participants exposed to these risk factors.

The reporting of this study will be prepared in accordance with the Strengthening the Reporting of Observational Studies in Epidemiology guidelines.^43^ Summary and descriptive statistics will be tabulated for all primary and secondary outcome variables, as well as for exposure variables and potential confounding or mediating factors. Time plots for all outcome variables will be inspected. Quantitative data analysis will be conducted to assess the primary outcomes.

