There will be three analysis time points: (1) after recruitment has finished and baseline data are available for all participants (baseline analysis); (2) once every participant has completed 6 months in the study (6-month analysis); and (3) at 36 months, when each participant has completed 24 months in the study (final analysis).

The baseline analysis will largely consist of descriptive statistics on participant characteristics and data recorded at baseline. Simple regression models will also be used to investigate relationships between exposure and outcome variables measured at baseline. Unadjusted analyses will consist of paired t-tests or Wilcoxon signed-rank tests (depending on whether the data are normally distributed or not) for continuously measured variables, and χ^2^ or Fisher’s exact tests (depending on contingency table cell counts) for binary and categorical variables. Adjusted analyses will be conducted using generalised linear models (GLMs).

The 6-month analysis will be limited in scope and serves two purposes: (1) characterise new-onset vasculopathy in HIV-infected participants who have initiated ART treatment at baseline (vascular IRIS) and (2) define vasculopathy outcomes for the final analysis. The main analysis of the study data will be conducted at the final analysis time point.

For objective 1 we will develop three regression models. Two GLMs will be developed to compare mean progression of arterial damage from baseline in HIV-infected ART patients and HIV-uninfected adults. These models will regress change from baseline PWV and CIMT, respectively, on HIV status. We will develop a third model to estimate the RR and population-attributable fraction of new-onset arterial damage in HIV-infected patients compared with HIV-uninfected adults.

For objective 2a, a set of GLMs will be developed to compare mean progression of vasculopathy in HIV-infected ART patients with and without reactivated latent herpes viral infection. These models will regress PWV and CIMT, respectively, on, on two log-transformed variables for antibody titres of CMV and VZV.

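### The objective 1 model alone cannot give a population-attributable fraction, because the cohort's HIV share (800 of 990) is set by design and no prevalence source is named

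*Protocol article*

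**What the plan says.** Under Sample size and statistical analysis, the objective 1 plan has two models for mean progression and a third for new-onset disease, which is to "estimate the RR and population-attributable fraction of new-onset arterial damage in HIV-infected patients compared with HIV-uninfected adults". This sentence is the only mention of a population-attributable fraction in the article, and it names neither a target population nor a source for the HIV prevalence.

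The cohort is described under Study design as a "prospective cohort study in 800 HIV-infected patients initiating ART and 190 HIV-uninfected adults aged ≥35 years", and there "HIV-infected and HIV-uninfected participants will be frequency-matched by 5-year age band and sex". Study setting shows that the two groups come from different sources: patients from ART clinics, and uninfected adults from pre-ART counselling sessions and randomly selected households. The group sizes come from the power calculation: "The required sample size for the study’s primary objectives is 800 HIV-infected patients and 190 HIV-uninfected adults".

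The planning values are "The minimum relative risk (RR) of interest is 2 for objective 1 and 1.8 for objective 2" and "we assume a 24-month cumulative vasculopathy risk of 9.2% in HIV-negative participants, 18.4% in all HIV-infected participants".

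The only population HIV prevalence in the article is background in the Introduction: "Countries such as Malawi have an adult HIV prevalence of approximately 10" per cent. It is not linked to the analysis.

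**The concern.** An RR compares risk between two groups and does not depend on how many people were enrolled in each. A PAF does depend on it, unless prevalence comes from elsewhere: it is the share of all cases in a population that would not occur without the exposure, so it rises with the proportion exposed. In this cohort that proportion was chosen to achieve power. Enrolling more controls would lower a PAF computed from the cohort with no change in biology.

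The article assigns the PAF to the regression model, and the only HIV share in that model's data is the one the design created. A PAF built on that share describes no real population. At stake is the reading of one objective 1 estimate: whether HIV appears to account for nearly half of new-onset arterial damage or for a much smaller part.

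**Working it through.** **Inputs from the article.** Enrolment 800 and 190; RR 2 for objective 1; 24-month risks 18.4% (HIV-infected) and 9.2% (HIV-negative); 18.4% of HIV-infected participants excluded for abnormal baseline pulse wave velocity; 20% loss to follow-up in both groups; adult HIV prevalence about 10%. All other prevalences and RRs below are assumptions, used to show a range.

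**1. Reproducing the plan's own figure.** The article gives no PAF value, but the objective 1 sample size can be checked.
- Analysable numbers: 190 × 0.8 = 152 controls; 800 × 0.8 × 0.816 = 522 HIV-infected.
- The normal approximation with pooled variance under the null, two-sided 0.05, no continuity correction, gives power of 80.8%. At this ratio 150 analysable controls are needed, and 150/0.8 = 188 against the 190 stated.

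So the RR of 2 and the two risks are confirmed as the planning values. (That the power and the HIV share are both 80.8% is coincidence.)

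**2. HIV share in the cohort.** p = 800/990 = 0.808.

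**3. PAF at RR 2.** Levin's formula: PAF = p(RR − 1) / [1 + p(RR − 1)].
- Cohort share: 0.808/1.808 = 44.7%.
- 10% prevalence: 0.10/1.10 = 9.1%.
- Ratio: 44.7/9.1 = 4.9.

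**4. Check from the risks.** PAF = (overall risk − risk in unexposed) / overall risk.
- Cohort: overall risk = 0.808 × 18.4% + 0.192 × 9.2% = 16.63%; (16.63 − 9.2)/16.63 = 44.7%.
- 10% prevalence: overall risk = 0.10 × 18.4% + 0.90 × 9.2% = 10.12%; (10.12 − 9.2)/10.12 = 9.1%.

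**5. Using the exposed share among cases does not avoid the problem.** Expected cohort cases are 800 × 0.184 = 147.2 and 190 × 0.092 = 17.5, so 147.2/164.7 = 89.4% of cases are HIV-infected. Then 0.894 × (RR − 1)/RR = 0.894 × 0.5 = 44.7% again.

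**6. Dependence on the design.** With 800 controls instead of 190, p = 0.5 and the cohort PAF would be 0.5/1.5 = 33.3%, at the same RR and the same risks.

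**7. Sensitivity to prevalence at RR 2.** Cohort-share PAF 44.7% throughout:

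| Population HIV prevalence | PAF | Ratio to 44.7% |
|---|---|---|
| 5% (assumed) | 4.8% | 9.4 |
| 10% (Introduction) | 9.1% | 4.9 |
| 15% (assumed) | 13.0% | 3.4 |
| 20% (assumed) | 16.7% | 2.7 |
| 25% (assumed) | 20.0% | 2.2 |

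**8. Sensitivity to RR at 10% prevalence.** RR 1.5 (assumed): 28.8% against 4.8%, ratio 6.0. RR 3 (assumed): 61.8% against 16.7%, ratio 3.7.

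**9. Analysable rather than enrolled share.** 522/(522 + 152) = 0.775; at RR 2 the PAF is 522/(674 + 522) = 0.436, or about 44%, and the ratio to 9.1% is 4.8. The exclusions barely matter.

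**10. Attributable fraction among the exposed.** (RR − 1)/RR = 1/2 = 50% at RR 2. No prevalence is needed.

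**The case against.** The strongest reply is that the article never says the cohort's HIV share will be used. Combining a cohort RR with an external prevalence is standard and compatible with the sentence, and a full protocol or analysis plan, not shown here, may specify it. This stands. A reader might infer that the plan will report a PAF of about 45%, but the text does not support that: it is silent on prevalence, so the figure can only be conditional.

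Second, the phrase comparing HIV-infected with HIV-uninfected participants may describe the attributable fraction among the exposed, which needs no prevalence. This also stands as a possible reading. On it there is no numerical error, only a misleading name.

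Third, a reader might take five-fold as the size of the error. That figure rests on a national all-adult prevalence cited as background, not on one for adults aged ≥35 in Blantyre, and step 7 shows how far it moves.

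Fourth, the PAF is mentioned once and is absent from the abstract, the objectives, the outcomes and the sample size. The RR and the progression models, which carry objective 1, do not depend on the 800:190 ratio for validity. This limits the importance of the point. Frequency matching and the 15% cap on ages 35–39 also shape the age mix, but they do not produce the 81% share.

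The objection does not reduce the point to a detail left for a fuller document. The sentence ascribes to a model a quantity that the design cannot identify, or gives a different quantity the wrong name. Either way it needs correcting.

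**Conclusion.** The point holds in a conditional form. The cohort's 80.8% HIV share is a design choice, so a model of this cohort can estimate the RR but cannot by itself identify a PAF for any real population, and the article names no prevalence source. If the cohort share were used, the PAF would be overstated about five-fold at RR 2 and 10% prevalence, and about two- to nine-fold at RR 2 over assumed prevalences of 25% to 5%. These sizes rest on the planning RR and on prevalences that, apart from the 10%, are assumed. If the attributable fraction among the exposed is intended, the calculation is sound and the label is not. This is a worthwhile correction to one secondary quantity within objective 1, not a threat to the primary comparison.

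**What to change.** Replace the sentence so that the third model estimates the adjusted RR and the attributable fraction among HIV-infected participants, (RR − 1)/RR, each with a confidence interval, and call the latter by that name.

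Keep a PAF only if the plan:
- names the target population, for example adults aged ≥35 in the clinics' catchment area;
- names an external source of HIV prevalence for that population, preferably by age and sex, and does not use the cohort's exposure mix;
- combines that prevalence with the adjusted RR and carries the uncertainty of both into the interval;
- states that the RR comes from people starting ART without a history of cerebrovascular or cardiovascular disease, so that applying it to everyone living with HIV is an assumption.

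The cost is a sentence or two, one external input, and a reported fraction that will probably be smaller than one taken from the cohort. Recruitment, sample size, data collection and the RR analysis do not change.

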### Study objectives

This study will test the hypothesis that immune activation and dysfunction, driven by HIV and reactivation of latent CMV/VZV herpesvirus infections, lead to increased CBD/CVD risk in adults aged ≥35 years in SSA. We will address this through the following objectives:

To determine if progression of the surrogate marker of CBD/CVD or occurrence of new-onset vasculopathy is higher in adults aged ≥35 years with HIV infection on ART compared with those without HIV.To determine if progression of surrogate markers of CBD/CVD or occurrence of new-onset vasculopathy is higher in adults aged ≥35 years with HIV/herpes viral antigenaemia or chronic immune activation compared with those without HIV/herpes viral antigenaemia or chronic immune activation. Specifically, we will determine if progression of surrogate markers or new-onset vasculopathy is higher in the following:In ART patients with reactivated latent herpes viral infection, compared with those without reactivated latent herpes viral infection.In ART patients with the highest 25% of markers for immune activation, inflammation or endothelial activation compared with the bottom 25%.In ART patients with incomplete virological suppression or virological resurgence of HIV, compared with those with suppressed HIV plasma viral load.

The secondary study objectives are to determine if viral antigenaemia or chronic immune activation increases the occurrence of the following clinical events: (1) stroke, (2) MI, (3) angina (excluding MI), (4) peripheral vascular disease (PVD), (5) all-cause death/vascular-related death and (6) immune reconstitution inflammatory vasculopathy.

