### Study participants

Study inclusion criteria will be (1) age ≥35 years and (2) resident of Blantyre. HIV-infected patients must further be (3) ART-naïve or initiated ART <10 days prior to enrolment and (4) initiating standard first-line ART. Adult controls must further be (5) HIV-uninfected. Study exclusion criteria are (6) clinical history of CBD/CVD, (7) pregnancy, (8) critical illness or symptomatic anaemia at baseline, and (9) enrolment in an intervention study. At the analysis stage abnormal pulse wave velocity (PWV) at baseline (as defined in table 2) will be excluded for new-onset vasculopathy analysis but not for progression of vasculopathy. The same approach will be applied for baseline carotid intima-media thickness (CIMT) measurements. If the study participant becomes pregnant after recruitment, they will be withdrawn.

**Table 2 T2:** Case definitions of primary and secondary endpoints for the study

Type	Definitions
Primary endpoint	Carotid intima-media thickness (CIMT)	*The occurrence of new-onset vasculopathy**(**CIMT, a measure of atherosclerosis**)*: CIMT >0.9 mm or >75th percentile of age/sex references values or presence of plaque on the carotid scan. *Progression*: total change in CIMT at 24 months from baseline.
	Pulse wave velocity (PWV)	*Occurrence of new-onset vasculopathy**(**PWV*,*a measure of arterial stiffness**)*: PWV >12 (m/s). *Progression*: total change in PWV at 24 months from baseline.
Secondary endpoint	Stroke	*Confirmed (**1**+**2**) or 3 or 4 or 5:* Acute onset with a clinically compatible course, including unequivocal objective findings of a localising neurological deficit. CT or MRI compatible with a diagnosis of stroke and current neurological signs and symptoms. Stroke diagnosed as the cause of death at autopsy. Clinical history and positive lumbar puncture compatible with subarachnoid haemorrhage. Death certificate or death note from medical record listing stroke as the cause of death.

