For objective 2b, we will again fit a set of GLMs, with change from baseline in PWV as response variable, this time to investigate if, in HIV-infected ART patients, there is an association between progression of vasculopathy and immune activation and inflammation biomarkers (IL-6, Intracellular adehesion molecule [ICAM], CD163). Specifically, for each marker, we will regress PWV on marker quantiles. After having built models for each marker, we will then develop comprehensive multiple regression models for PWV and CIMT with multiple independent markers as predictor variables.

For objective 2c, we will proceed as for objective 2a, but comparing HIV-infected ART patients with incomplete virological suppression or virological resurgence of HIV with those with suppressed HIV plasma viral load.

In addition to these analyses, given the repeated measurements for PWV, immune activation and inflammation markers, we will extend the GLMs for PWV to linear mixed models taking full account of the longitudinal nature of the data. Mixed models will also handle deviations from the visit schedule in a principled fashion and use all available data for dropouts. If a log link function is required for PWV in the GLMs, we will fit marginalised models using Generlaised Estimating Equations [GEE] instead of Linear Mixed Models [LMMs].

For the secondary study objectives, we will use univariate methods to assess the frequency of clinical events within exposure strata. If there are sufficient numbers of clinical events, we will develop Poisson or negative binomial regression models (depending on model fit) for each clinical event type to compare exposure-defined participants.

We will also use time-to-event models, specifically Cox proportional hazard models, to investigate associations between all-cause mortality and exposures.

As part of exploratory analyses, we will aim to identify risk groups that are potentially incompletely captured with the measured exposure variables. We will perform unsupervised group-based multitrajectory modelling of multivariate longitudinal patient trajectories to confirm any associations we have found using more traditional approaches.^44^

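### The stated response for the objective 2a and 2c models is PWV and CIMT, not their change from baseline, which conflicts with the models' own purpose, with Table 2 and with objective 1; objective 2b is inconsistent on the same point

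*Protocol article*

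**What the plan says.** All references are to the protocol article.

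- **Study objectives.** Objective 2 asks whether progression of the surrogate markers, or new-onset vasculopathy, is higher in exposed patients. For 2a the contrast is "In ART patients with reactivated latent herpes viral infection, compared with those without reactivated latent herpes viral infection".
- **Table 2 (under Study participants).** Progression of PWV is the "total change in PWV at 24 months from baseline". CIMT progression is defined in the same way.
- **Sample size and statistical analysis, objective 1.** "These models will regress change from baseline PWV and CIMT, respectively, on HIV status".
- **Same section, objective 2a.** The models are meant to "compare mean progression of vasculopathy in HIV-infected ART patients with and without reactivated latent herpes viral infection". The next sentence gives the model: "These models will regress PWV and CIMT, respectively, on, on two log-transformed variables for antibody titres of CMV and VZV".
- **Same section, objective 2b.** The response is first given as change from baseline in PWV. Then: "Specifically, for each marker, we will regress PWV on marker quantiles". The paragraph ends with multi-marker models for PWV and CIMT, with no mention of change.
- **Same section, objective 2c.** "For objective 2c, we will proceed as for objective 2a".
- **Same section, longitudinal extension.** The PWV models are to be extended to linear mixed models. GEE is the fallback: "If a log link function is required for PWV in the GLMs". No extension is given for CIMT.

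**The concern.** Objectives 2a and 2c are primary objectives about progression. The one sentence that specifies their model names a level as the response, with no change score and no baseline term. A regression of the 24-month level on titre tests whether mean PWV differs by titre. The objective asks whether mean change in PWV differs by titre. The two questions have different answers whenever exposure is related to PWV or CIMT before follow-up starts.

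Such a relation is plausible here. The study's hypothesis is that HIV and herpesvirus reactivation cause vasculopathy, and patients enrol at ART initiation, after exposure has begun. The sample-size section assumes that 18.4% of HIV-infected participants have abnormal PWV at baseline, and the Study participants section keeps such participants in the progression analysis. Under a literal level model, a difference already present at enrolment, including one due to confounding or reverse causation, could be reported as an effect on progression.

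**Working it through.** **1. The plan's own figure, and whether it depends on this point.** The sample size uses the binary new-onset outcome. With unexposed risk 0.159, exposed risk 0.286, exposed:unexposed ratio k = 0.25, two-sided α = 0.05 and 80% power:

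- Pooled risk: 0.8 × 0.159 + 0.2 × 0.286 = 0.1844.
- n unexposed = [1.96 √(0.1844 × 0.8156 × (1 + 1/k)) + 0.8416 √(0.159 × 0.841 + 0.286 × 0.714/k)]² / (0.286 − 0.159)² = (1.700 + 0.821)² / 0.01613 ≈ 394.
- Total: 394 × 1.25 = 492.5. Divided by (1 − 0.184 − 0.20) = 0.616, this is 799.5, against 800 stated.
- The same formula for objective 1 (9.2% against 18.4%, about 493 evaluable HIV-infected patients) gives 151 controls; 151/0.8 = 189, against 190 stated.

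The figures reproduce and do not depend on whether the continuous response is a level or a change.

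**2. The response, model by model.**

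| Model | Stated purpose or endpoint | Stated response |
|---|---|---|
| Objective 1 | Mean progression | Change from baseline, PWV and CIMT |
| Objective 2a | Mean progression | PWV and CIMT |
| Objective 2b, opening | Progression | Change from baseline, PWV only |
| Objective 2b, detail | Progression | PWV |
| Objective 2b, multi-marker | Progression | PWV and CIMT |
| Objective 2c | As 2a | As 2a |

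Change in CIMT is not named as a response in any objective 2 model. Table 1 schedules CIMT at baseline and 24 months only, so for CIMT in 2a and 2c the sentence in question is the whole model specification.

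**3. What would follow if levels were modelled (illustration).** From the documents: 800 patients and 20% loss, so 800 × 0.8 = 640. The 18.4% exclusion is not applied, because it does not apply to progression. Assumed: PWV SD of 2 m/s at both visits, correlation r between titre and baseline PWV, and change truly unrelated to titre. The 24-month level then also correlates r with titre, and the test statistic is centred at

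λ = √n × r / √(1 − r²), with rejection probability ≈ Φ(λ − 1.96) + Φ(−λ − 1.96).

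| r | λ at n = 640 | Level model, formula | Level model, simulation | Change model |
|---|---|---|---|---|
| 0.05 | 1.27 | 24% | 24% | about 5% |
| 0.10 | 2.54 | 72% | 69% | about 5% |
| 0.15 | 3.84 | 97% | 96% | about 5% |

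The simulation used 4,000 replicates per cell and allowed for regression to the mean. At n = 522 the simulation gives 20%, 61% and 92%, and the formula 21%, 63% and 93%.

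A second illustration used a binary exposure (20% exposed, n = 522, SD 1, within-person correlation 0.6), a baseline difference of 0.5 SD and equal progression. The level model rejected in 99% of runs and the change model in 4.5%.

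**The case against.** The strongest reply is that the article supplies the missing words itself. The sentence just before the 2a model says that progression is compared, and Table 2 defines progression as change. The 2b paragraph states change from baseline as the response and then describes that same model as regressing PWV, so the authors evidently use the short form for a change model. The 2a sentence also carries a repeated word, which fits an unedited slip. This stands, and it makes a drafting omission the likeliest reading. A reader might infer that the investigators have chosen to analyse levels and that the 2a and 2c results will be invalid. The documents do not establish that.

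The reply does not settle the matter, for two reasons. First, a log link is foreseen for PWV in the GLMs. A log link needs a positive mean, which PWV always has and mean change need not have. The clause is conditional and sits among the repeated-measures models, so it is weak evidence for levels, but it keeps the question open. Second, the 2b text names change for PWV only, so it is no key to the CIMT models.

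A reader might also infer that a level model would lose power to detect real progression. That is not supported in general. Take a titre that correlates 0.11 with change and 0 with baseline, n = 640, and about 80% power for the change model. With SD of change 1.0, 1.5 and 2.0 m/s, the level model has 24%, 39% and 51% power if change is independent of baseline. If the PWV SD stays at 2 m/s, it has about 29%, 55% and 80%. The loss depends on assumptions that the documents do not fix, so no claim is made on it.

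Finally, the exact time terms of the mixed models are commonly left to a statistical analysis plan. Their absence from the article is not counted here.

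**Conclusion.** The point holds as an inconsistency in how a primary analysis is specified, not as proof that the wrong analysis is planned. The stated response for 2a, and through it 2c, conflicts with the stated purpose of those models, with Table 2 and with objective 1, and 2b is inconsistent within one paragraph. If the sentence were followed literally, a baseline difference could be reported as faster progression: in roughly 24% to 96% of studies for assumed correlations of 0.05 to 0.15 at n = 640, against 5% for a change model.

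Those figures rest on the assumed correlations, on the literal level reading with no baseline term, and on change being unrelated to titre. The last assumption gives the change model its 5% by construction. The SD of 2 m/s is also assumed; in the formula only its constancy between visits matters. The exposure is greatest for CIMT. The sample size and power statements are unaffected.

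**What to change.** In Sample size and statistical analysis:

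- For objectives 2a, 2b (including the multi-marker models) and 2c, state that the response is the change from baseline to 24 months in PWV and in CIMT, as in objective 1 and Table 2.
- State that any log link applies to the PWV level in the longitudinal models and not to the change score.

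The cost is a change of wording. Table 1 already schedules PWV and CIMT for ART patients and controls at baseline and 24 months, so no new data are needed. The benefit is that nobody has to choose, after the data are in, between two analyses that can reach opposite conclusions on a primary objective.
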